#### Secondary outcome measures

*Secondary outcome measures* are assessed by interview or self-report. They include the following measures.

### Diagnosis of depression and psychiatric comorbidity

Diagnosis of depression and psychiatric comorbidity will be assessed using the German version of the Structural Clinical Interview for DSM-IV (SCID-I and II-Interview) (56, 57). The SCID used in this study will be based on the DSM-IV classification system (58), as the German version of the SCID for DSM-5 is not yet available. Also, a structured assessment of diagnosis and course of depression (59) will be conducted.

### Severity of depression

Severity of depression will be assessed using the HRSD described above as well as the Quick Inventory of Depressive Symptoms (QIDS-C16) (60) and the Patient Health Questionnaire (PHQ-9) (61). All three measures have good psychometric qualities and are sensitive to change (47, 62, 63).

### General psychopathology

General psychopathology will be assessed using the Brief Symptom Inventory (BSI) (64), a short form of the SCL-90-R, which shows good psychometric properties (65).

### General psychosocial level of functioning and participation

General psychosocial level of functioning and participation will be assessed using the WHO Disability Assessment Schedule 2.0 (WHODAS 2.0) (66). The WHODAS 2.0 measures functioning and disability in major life domains (communication and understanding, getting around, self-care, getting along with others, life activities and participation in society). Quality of life will be assessed using the Short Form-12 Health Survey (SF-12) (67).

### Difficulties in emotion regulation skills

Difficulties in emotion regulation skills will be assessed using the Difficulties in Emotion Regulation Scale (DERS) (68). The DERS has high internal consistency, good test-retest reliability and adequate predictive and construct validity (68).

### Traumatic experiences

Traumatic experiences will be assessed only once before start of treatment using the Childhood Trauma Questionnaire (CTQ) (69, 70), which assesses five domains of childhood maltreatment experiences (emotional abuse, physical abuse, sexual abuse, emotional neglect, physical neglect). Both the original and the German version have good psychometric properties (69, 70).

### Care dependency

Care dependency will be assessed using the Care Dependency Questionnaire (CDQ). The CDQ is a reliable and valid questionnaire that measures patient's care dependency. The questionnaire consists of three unidimensional subscales (submissive dependency, need for contact, lack of perceived alternatives) (71).

### Therapists' demographic variables

Therapists' demographic variables will be assessed using the Therapeutic Attitude Scale (ThAt). This questionnaire has been developed by Sandell et al. (ThId) (72) and has been translated into German by Klug et al. (ThAt) (73, 74). In this study, sections A and B of the ThAt, will be used, which assess demographic variables as well as education, supervision and experience.

### Method-specific measures

Method-specific measures will be the Major Depressive Disorder Scale (MDD-S) (22), the Metacognitions Questionnaire (MCQ-30) (67) and the Response Style Questionnaire (RSQ-D) (75) to assess metacognitions, rumination and worry. The Behavioral Activation of Depression Scale (BADS) (76) will be used to assess the degree of behavioral activation.

### Process parameters

The MDD-S, the BADS and the self-rating version of the QIDS (QIDS-SR16) will be used as process parameters. In the MCT condition, the QIDS-SR16 and the MDD-S will be assessed weekly and the BADS monthly. In the BA condition, the QIDS-SR16 and the BADS will be assessed weekly and the MDD-S monthly.

### Psychopharmacological treatment and demographic parameters

Psychopharmacological treatment and demographic parameters will be assessed using a medication questionnaire and a demographic questionnaire.

### Treatment retention

Treatment dropouts are defined as patients who discontinue treatment before remission but agree to be assessed at the planned assessment time points. Study dropouts are patients who drop out of both treatment and assessment. Patients who withdraw their informed consent to participate in the study are study dropouts but may continue treatment as planned. Patients remitted at the mid-treatment assessment (after 3 months of treatment) can end therapy early and are considered “early successes.” Mid-treatment assessment will then be replaced by post-treatment assessment.

### Statistical analyses

Hypothesis will be tested by performing analyis on the whole database including all randomized patients (intention-to-treat analysis). Multiple imputation procedure will be used to replace missing data. We will use linear mixed models (LMM) as they have the advantage of using all available data of each subject. LMM analyses also offer the opportunity to choose an appropriate covariance structure reflecting the potential dependence due to repeated measurements (77). Adjustment for baseline measure will be chosen as this increases statistical power and accounts for regression to the mean (78). All continuous outcomes will be analysed as change from baseline with a random intercept for the participant, time as within-groups factor, study group as well as gender as fixed effect and adjustment for baseline measure. The study hypothesis will be tested on the main effect for group. The estimation of effect size will be based on the imputated dataset and Cohen's d will be calculated for continuous data and numbers needed to treat (NNT) for binary data. The appropriate forms of mixed regression will be chosen for categorical outcome variables, counts and in case of non-normal residuals (poisson, gamma, negative binominal, etc.). To identify predictors or moderators related to treatment outcome, mixed regression methods will be used.

Negative effects will be identified by analyzing and reporting the amount of participants that experienced a clinical significant deterioration [according to Jacobson and Truax (79)].For the time to event analysis, onset of remission will be used as the dependent variable and group assignment as the independent variable. Here, remission will be defined as a score of < 6 on the weekly QIDS-SR16 rating. Patients who do not achieve remission within the 6 months of treatment or dropped out will be censored. No missing data will be substituted for this analysis. The *Kaplan-Meier method* will be used to estimate time to remission (in weeks) and remission rates. The main hypothesis will be tested by comparing the estimated remission rates in both groups using the log-rank test. *Cox proportional hazards regression* will be used to calculate the hazard ratios, to evaluate the influence of covariates for the adjusted analyses and to perform the subgroup analyses.

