### Sample size

The primary outcome measure to test the main hypothesis is the severity of depressive symptoms at post-treatment, assessed by the Hamilton Rating Scale for Depression [HRSD, 24-items version (47)]. Confirmatory two-tailed testing of two conditions requires a sample size of *n* = 64 patients in each condition (total *N* = 128 patients). The sample size calculation (48) is based on a power of 80% and a type I error of 5%, as well as an effect size of *d* = 0.5. The estimated between subjects effect size is set according to the one defined by the National Institute of Clinical Excellence (49) for clinical significant difference (*d* ~ 0.5).

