### Intervention

Participants will be randomized to either MCT or BA treatment. The structural conditions in both treatment programs are as similar as possible to guarantee clinical equipoise. In both conditions, treatment duration will be a maximum of 6 months with one individual therapy session (50 min) and one group therapy session (90 min) per week. Patients remitted at the mid-treatment assessment (after 3 months of treatment) can end therapy early. After the 12 months follow up assessment, participants see their study therapist for an evaluation session in which the results of the assessment are discussed and in which further treatment will be planned if necessary. Patients will receive 1–2 individual sessions before the start of group treatment to become accustomed to the treatment model and their therapist and to be prepared for the group sessions. The estimated amount of sessions in the program will be 20–24 individual sessions and 24 group sessions. To date, there is little research on the difference between the effectiveness of combined group and individual therapy vs. individual or group therapy only. For several reasons, we decided to offer a combined group and individual therapy program based on our clinical experience: Adding a weekly group therapy session to weekly individual sessions has the advantage of being able to offer psychoeducation and training of specific skills in a group setting, which leaves enough room in the individual sessions to address personal issues and special needs of the patients. Also, as inclusion takes place every 3 months and treatment duration is 6 months, patients that are new to the group can learn from the patients that have already completed 3 months of treatment. As patients treated in the University Hospital display high chronicity, comorbidity and complex symptomatology, we considered group therapy only to be insufficient.

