A limitation of the PRO^*^MDD study is that a two-sided primary hypothesis was used instead of a superiority hypothesis of one therapy method or a non-inferiority hypothesis. The reason for choosing a two-sided hypothesis is based on the fact that there is no prior data that justifies a superiority hypothesis of one method above the other, and that for a non-inferiority trial, the power of this study is not expected to be sufficient. As this is the first study to compare BA and MCT for patients with MDD, it intends to generate pilot data for orientation and hypothesis generation for future research to build upon. The sample size was calculated to detect differential treatment effects of a medium effect size. As both treatment methods are known to be effective, between-group differences may be small and therefore not reach statistical significance. Nevertheless, this study will contribute to building a database of comparisons of treatments for MDD which can be used to identify differences in treatment methods using meta-analytic techniques. A further limitation is that the study does not include a control group such as waitlist-control or treatment as usual. Therefore, non-specific factors such as time cannot be controlled for. We decided against an inactive control group for ethical reasons; as most patients treated in this study setting display complex symptomatology, high comorbidity and chronicity, we will try to minimize the time until they can access treatment. Also, a control group with no treatment or treatment as usual might increase resistance of patients and therapists to participate in the trial and this might endanger the representativeness of the study group and the practicability of patient recruitment. Another issue that needs to be discussed is the different treatment durations recommended for the treatment methods. In most MCT studies, treatment duration is a maximum of 10–12 sessions whereas initial studies of BA included up to 24 sessions (36, 80). To guarantee equipoise of the treatment framework, a maximum of 20–24 individual sessions and 24 group sessions is offered to patients in both treatment conditions. In case of early remission, discontinuation of treatment is possible at mid-treatment (after approximately 10–12 sessions). As previous research has shown that a small number of MCT sessions can already lead to substantial improvement in depressive symptoms, it is hypothesized that MCT will lead to a faster symptom reduction than BA.

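### The primary outcome and the sample size refer to HRSD-24 at post-treatment, but the hypothesis is tested on a group main effect that pools over the modelled visits

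*Protocol article*

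**What the plan says.** The Sample size section of the protocol article fixes outcome and time point: "The primary outcome measure to test the main hypothesis is the severity of depressive symptoms at post-treatment". The measure is the 24-item HRSD. The section describes the test as "Confirmatory two-tailed testing of two conditions" and the calculation as "based on a power of 80% and a type I error of 5%, as well as an effect size of *d* = 0.5", giving 64 per arm and 128 in total.

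The Statistical analyses section describes one linear mixed model for all continuous outcomes. The response is change from baseline with a random intercept per participant, and the other terms are "time as within-groups factor, study group as well as gender as fixed effect and adjustment for baseline measure". No group-by-time term is named. The next sentence states the test: "The study hypothesis will be tested on the main effect for group". The section does not say which visits are modelled, but gives the use of all available data per patient as a reason for choosing mixed models.

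Table 2 in the Assessments section marks the HRSD at baseline, pre-treatment, 3, 6, 12, 18 and 30 months. Under Treatment retention, patients remitted at mid-treatment may stop therapy, and their mid-treatment assessment is then replaced by the post-treatment assessment.

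**The concern.** With time as a factor and no interaction, the model assumes the same group difference at every visit and estimates it with one coefficient. If the true differences vary, the coefficient estimates their average, not the difference at post-treatment.

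The protocol gives reasons to expect variation. The Discussion says that "it is hypothesized that MCT will lead to a faster symptom reduction than BA", which implies a gap that changes over time. The Intervention section schedules a session after the 12-month assessment "in which further treatment will be planned if necessary", so the 18- and 30-month ratings may partly reflect later care. If the pre-treatment visit is modelled as an outcome, it adds a time at which no study therapy has been given.

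A real post-treatment difference could therefore be diluted and missed. Equally, a difference confined to other visits could be reported as a positive primary result. If the wording stays open, the choice between two different primary results could also be made after the data are seen.

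**Working it through.** **1. The plan's own figure.** Inputs from the Sample size section: d = 0.5, two-sided 5%, power 80%. A two-sample t test at one time point (noncentral t) has power 0.795 with 63 per arm and 0.801 with 64. The stated 64 per arm is correct, and it is a single-time-point calculation without baseline adjustment.

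**2. What the planned test estimates.** For k modelled visits with complete data and equal correlations, the group coefficient estimates the mean of the k visit-specific differences. Change from baseline with adjustment for baseline gives the same group coefficient as the follow-up score adjusted for baseline.

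**3. Assumptions, which the documents do not supply.** SD 1 at each visit; the same correlation ρ between all visits including baseline (compound symmetry), ρ = 0.5; 64 per arm; no dropout; and the effect profiles shown below.

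**4. Formula.** The baseline-adjusted variance of a patient's mean over k visits is v = (1 + (k − 1)ρ)/k − ρ². The standardised effect is the mean difference divided by √v. Power is that of a two-sided 5% two-sample test with 64 per arm.

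For ρ = 0.5:
- k = 1: v = 1 − 0.25 = 0.75, √v = 0.866
- k = 2: v = 0.75 − 0.25 = 0.50, √v = 0.707
- k = 5: v = 0.60 − 0.25 = 0.35, √v = 0.592
- k = 6: v = 0.583 − 0.25 = 0.333, √v = 0.577

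| Quantity tested | Differences d at the modelled visits | Mean d | Mean/√v | Power |
|---|---|---|---|---|
| Post-treatment contrast | 0.5 | 0.50 | 0.577 | 90% |
| Average, 3 and 6 months | 0.25, 0.5 | 0.375 | 0.530 | 84–85% |
| Average, 3 and 6 months | 0, 0.5 | 0.25 | 0.354 | 51–52% |
| Average, 3 to 30 months | 0.25, 0.5, 0.35, 0.2, 0.1 | 0.28 | 0.473 | 76% |
| Same plus pre-treatment | 0, 0.25, 0.5, 0.35, 0.2, 0.1 | 0.233 | 0.404 | 62–63% |
| Average, 3 to 30 months | 0, 0.5, 0, 0, 0 | 0.10 | 0.169 | 16% |
| Average, 3 to 30 months | 0.5 at all five | 0.50 | 0.845 | above 99% |
| Average, 3 to 30 months | 0, 0, 0.4, 0.4, 0.4 | 0.24 | 0.406 | 62–63% (rejection) |

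Where two figures are shown, the first is from the noncentral t and the second from the normal approximation. In every row but the last, the post-treatment difference is 0.5. In the last row it is zero.

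**5. Sensitivity to ρ.** For ρ = 0.3, 0.5 and 0.7 the post-treatment contrast has 84%, 90% and 98% power (normal approximation). Over the range 0.3 to 0.7, the 3-and-6-month average with d = 0.25 and 0.5 has about 80% to 94%, and with d = 0 and 0.5 about 47% to 65%. The gap between the two tests does not depend on one choice of ρ.

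**The case against.** **The hypothesis itself has no time point.** The Introduction says only that the treatments differ in reducing depressive symptoms, and the Abstract and the primary outcome section name no visit either. A group main effect does address that wording. But the Sample size section ties the test of the main hypothesis to post-treatment and derives N there, so the two sections still disagree.

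**An article condenses the protocol.** The visit list may be in an analysis plan that is not shown. This limits the point: a reader might infer that all assessments through 30 months are averaged, and the text does not say so. The mismatch remains because the article names the tested effect explicitly, and an average over 3 and 6 months alone is still not the post-treatment difference.

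**The trial is called a pilot.** The Introduction and Discussion do describe hypothesis-generating data. This softens the consequence, but the Sample size section calls the test confirmatory.

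**Stronger readings that the documents do not support.**
- That the trial is underpowered. Power can be lower or higher than 80%. A constant effect raises it above 99%, and the 3-and-6-month average with d = 0.25 and 0.5 also keeps it at 80% or more once the planned baseline adjustment is counted.
- That the plan cannot examine whether MCT works faster. A time-to-remission analysis on the weekly QIDS-SR16 is planned for that question.
- That the covariance structure is wrongly fixed. The section leaves room to choose an appropriate one.

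**Conclusion.** The concern holds as a conflict between two explicit statements: the endpoint and its sample size refer to post-treatment, while the test refers to a difference pooled over unlisted visits. The sample size arithmetic is correct for the endpoint, but the 80% does not describe the planned test. For the same post-treatment effect of d = 0.5, the power of the averaged test runs from about 16% to above 99% in the profiles shown, against about 90% for a baseline-adjusted post-treatment contrast. With no post-treatment difference and d = 0.4 at each follow-up, it rejects in about 63% of trials.

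These sizes rest on the assumed effect profiles, compound symmetry, ρ = 0.5 and no dropout. The mismatch itself rests on none of them. It should be resolved before the outcome data are analysed.

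**What to change.** In the Statistical analyses section, treat time as categorical, add group-by-time, and state that the study hypothesis is tested by the MCT–BA contrast in HRSD-24 at post-treatment, two-sided at 5%. Report the contrasts at the other visits as secondary, and do not model pre-treatment as an outcome time.

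State also how early successes enter this contrast. Their post-treatment rating falls at about 3 months, so post-treatment is not the same calendar visit for every patient.

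Alternatively, keep the main effect, redefine the primary endpoint as the average over a stated list of visits, and restate the power for that quantity.

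The first option changes only the analysis wording. It needs no new data and, before dropout, keeps at least the stated 80% power with 128 patients. Its cost is that if the effect is constant over visits, the averaged test would have had more power (above 99% against about 90% under the assumptions above).

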### Outcome measures

#### Primary outcome measure

*Primary outcome measure* is depressive severity assessed by the 24-item version of the Hamilton Rating Scale for Depression (HRSD-24) (47), a semi-structured interview measuring severity of all symptom domains of depression described by the DSM-IV over the last 7 days. The HRSD has shown good psychometric qualities (47, 53). A cutoff of 16 points has been defined as indicating the presence of a moderate depressive episode and a total score of ≥16 points will be handled as inclusion criterion in this study (54). Remission of depression is defined as an HRSD score of ≤ 8, response as a reduction of 50% in the baseline total score of the HRSD (46, 55) and a score of 15 or less, but of more than 8.

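### Patients may stop therapy at month 3 on HRSD remission, but time to remission counts only a weekly QIDS-SR16 below 6, so some early finishers may be censored because they are well

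*Protocol article*

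**What the plan says.** All references are to the protocol article.

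- **General definition of remission** (Primary outcome measure): "Remission of depression is defined as an HRSD score of ≤ 8", rated by interview.
- **Early end of therapy** (Intervention, and again under Treatment retention): "Patients remitted at the mid-treatment assessment (after 3 months of treatment) can end therapy early". Treatment retention labels these patients early successes and has their mid-treatment assessment replaced by the post-treatment one. Treatment dropouts are defined there as stopping before remission, so early successes are not dropouts.
- **Event for time to remission** (Statistical analyses): "Here, remission will be defined as a score of < 6 on the weekly QIDS-SR16 rating".
- **Censoring and missing data** (Statistical analyses): "Patients who do not achieve remission within the 6 months of treatment or dropped out will be censored", and "No missing data will be substituted for this analysis".
- **Where the QIDS-SR16 is collected** (Process parameters): "In the MCT condition, the QIDS-SR16 and the MDD-S will be assessed weekly and the BADS monthly". The BA arm also has it weekly. Table 2 lists the clinician-rated QIDS-C16 but has no row for the self-rated QIDS-SR16.
- **Purpose** (Introduction, last paragraph; Discussion): the analysis is there because MCT is said to bring remission quickly, and the Discussion expects faster symptom reduction under MCT.

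**The concern.** One instrument decides who may leave therapy and another defines the event. They differ in rater (interviewer against patient) and in timing (at 3 and 6 months against weekly), so they will not always agree. A patient can be remitted on the HRSD at month 3 without having scored below 6 on the QIDS-SR16.

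Suppose that patient ends therapy and the weekly ratings end too. He or she then has no event and no later rating on which one could occur, and is not a dropout. The only status left is censored. Observation stops because the patient is doing well, so the chance of a later QIDS-SR16 remission is probably not that of patients still under observation. The planned survival methods assume that it is.

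What is at stake is the MCT-BA comparison of speed of remission, a secondary analysis but the one that addresses a stated expectation about MCT.

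**Working it through.** **The plan's own figure.** The article states no event rate or power for the time-to-event analysis. Its one sample-size figure, for the primary HRSD comparison, reproduces: d = 0.5, two-sided 5%, 80% power gives 63.77 per arm by the two-sample t-test, so 64. Nothing below affects it.

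**How many patients.** The article gives no rates, so these are assumptions: 20% to 40% of 128 HRSD-remitted at month 3, and 5% to 30% of those never below 6 on the QIDS-SR16.

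- Low: 128 × 0.20 × 0.05 = 1.3
- High: 128 × 0.40 × 0.30 = 15.4

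A simulation with assumed HRSD/QIDS correlations of 0.6 to 0.9 and 12 weekly ratings gave roughly 4 to 12 of 128. Ending therapy is optional, so the number who actually leave would be smaller.

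**Effect on the between-arm difference.** Assumed inputs:

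- QIDS-SR16 remission by week 13: 40% in MCT, 25% in BA.
- Of patients without that event, a share L is HRSD-remitted and leaves.
- By week 26, 70% of leavers and 25% of the others would have scored below 6 had all been rated.

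With p the week-13 remission rate:

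- Full observation: p + (1 − p) × [L × 0.70 + (1 − L) × 0.25]
- Leavers censored at week 13: p + (1 − p) × 0.25

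*Scenario A: L = 15% in MCT, 8% in BA.*

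- Leavers: 64 × 0.60 × 0.15 = 5.8 and 64 × 0.75 × 0.08 = 3.8
- Full, MCT: 0.40 + 0.60 × (0.105 + 0.2125) = 59.1%
- Full, BA: 0.25 + 0.75 × (0.056 + 0.230) = 46.5%
- Difference, full: 12.6 points
- Censored: 55.0% and 43.8%, difference 11.3 points
- Shift: 1.3 points towards no difference

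*Scenario B: L = 10% in both arms, all else the same.*

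- Leavers: 64 × 0.60 × 0.10 = 3.8 and 64 × 0.75 × 0.10 = 4.8
- Full, MCT: 0.40 + 0.60 × (0.070 + 0.225) = 57.7%
- Full, BA: 0.25 + 0.75 × (0.070 + 0.225) = 47.1%
- Difference, full: 10.6 points
- Censored: 55.0% and 43.8%, difference 11.3 points
- Shift: 0.7 points away from no difference

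The sign therefore depends on an input that the document does not give. A faster arm has more HRSD remitters but fewer patients still without a QIDS-SR16 event, and the net number of affected patients can go either way.

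**Against sampling error.** In scenario A the binomial standard error of the difference is √(0.5905 × 0.4095/64 + 0.4645 × 0.5355/64) = 0.088, or 8.8 points. The shift is 1.3/8.8, about 0.15 of a standard error.

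**The case against.** Several objections have weight.

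- **The separate definition is deliberate.** The statistical section marks it as specific to this analysis. During treatment the HRSD is taken only at 3 and 6 months, so it cannot time onset in weeks. This stands: choosing a weekly self-rating is sound, and having two definitions is not in itself a contradiction. The problem is how the event definition interacts with the right to leave.
- **The end of weekly ratings is inferred.** Table 2 omits the QIDS-SR16 even while patients are in therapy, so the missing row does not prove that ratings stop, and the Process parameters section gives no stopping point. This stands as a limit. Still, describing the scale as a process parameter of each treatment condition points that way, and nothing says that ratings continue.
- **The instrument for the early-stopping decision is not named** where the rule is given. The HRSD follows from the article's only general definition of remission.
- **A censoring date is detail for the analysis plan.** True of the date. But no date rule recovers ratings that were never collected, and data collection is fixed by the protocol.

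A reader might infer that early successes are counted as non-remitters. The document does not say so: under Kaplan-Meier a patient censored at the last rating leaves the risk set, and no sentence carries such patients event-free to 6 months. A reader might also infer that the analysis is biased against MCT or towards no difference. Scenario B shows that this does not follow.

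**Conclusion.** The point holds as a risk of informative censoring in the time-to-remission analysis. It rests on three readings: remission at mid-treatment means HRSD of 8 or less, the weekly ratings end with therapy, and some HRSD remitters who choose to leave have not yet scored below 6. The first two are implied by the text, not stated. The third is very likely but not documented: at 5% discordance among 20% to 30% remitters, the chance of at least one discordant patient is 74% to 86%.

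The direction is unknown and the size probably small: a few patients, and a shift in the between-arm difference of about 1 percentage point under assumed rates, well inside sampling error. The primary HRSD analysis and the sample size of 128 are unaffected. This is a cheap improvement, not a flaw that threatens the trial.

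**What to change.** 1. Collect the weekly QIDS-SR16 to week 26 in every randomised patient who agrees to assessment, whether or not therapy has ended, and list it in Table 2.
2. Keep QIDS-SR16 below 6 as the only event in the main analysis. Censor patients without an event at their last available rating, and amend the present sentence on censoring accordingly.
3. Add a sensitivity analysis that counts HRSD of 8 or less at the 3-month assessment as an event, dated to that assessment, for all patients in both arms who have no earlier QIDS-SR16 event. It must not be limited to those who leave: the event would then depend on the choice to leave, and an identical HRSD remitter who stays in therapy would get none. The HRSD is scheduled at both the mid- and post-treatment assessments, so relabelling the visit for early successes loses nothing.

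The cost is one row in Table 2, a few sentences in the analysis section, and about 3 more months of a short weekly self-rating for early finishers. Who may end therapy, and when, does not change.
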